## Abstract

**Background:**

Platelets stored at 1–6 °C are hypothesized to be more hemostatically active than standard room temperature platelets (RTP) stored at 20–24 °C. Recent studies suggest converting RTP to cold-stored platelets (Delayed Cold-Stored Platelets, DCSP) may be an important way of extending platelet lifespan and increasing platelet supply while also activating and priming platelets for the treatment of acute bleeding. However, there is little clinical trial data supporting the efficacy and safety of DCSP compared to standard RTP.

**Methods:**

This protocol details the design of a multicentre, two-arm, parallel-group, randomized, active-control, blinded, internal pilot trial to be conducted at two cardiac surgery centers in Canada. The study will randomize 50 adult (≥ 18 years old) patients undergoing at least moderately complex cardiac surgery with cardiopulmonary bypass and requiring platelet transfusion to receive either RTP as per standard of care (control group) or DCSP (intervention group). Patients randomized to the intervention group will receive ABO-identical, buffy-coat, pathogen-reduced, platelets in platelet additive solution maintained at 22 °C for up to 4 days then placed at 4 °C for a minimum of 24 h, with expiration at 14 days after collection. The duration of the intervention is from the termination of cardiopulmonary bypass to 24 h after, with a maximum of two doses of DCSP. Thereafter, all patients will receive RTP. The aim of this pilot is to assess the feasibility of a future RCT comparing the hemostatic effectiveness of DCSP to RTP (defined as the total number of allogeneic blood products transfused within 24 h after CPB) as well as safety. Specifically, the feasibility objectives of this pilot study are to determine (1) recruitment of ≥ 15% eligible patients per center per month); (2) appropriate platelet product available for ≥ 90% of patients randomized to the cold-stored platelet group; (3) Adherence to randomization assignment (> 90% of patients administered assigned product).

**Discussion:**

DCSP represents a promising logistical solution to address platelet supply shortages and a potentially more efficacious option for the management of active bleeding. No prospective clinical studies on this topic have been conducted. This proposed internal pilot study will assess the feasibility of a larger definitive study.

**Trial registration:**

NCT 06147531 (clinicaltrials.gov).

## Background

Platelets are one of the most commonly used blood products and as such are frequently in short supply. Currently, platelets are stored at room temperature (20–24 °C) to retain post-transfusion circulatory longevity but at the cost of reduced shelf-life, which is part of the reason for the supply challenges. Cold storage (at 1–6 °C) of platelets prolongs their shelf-life while maintaining hemostatic effectiveness in acutely bleeding patients. Thus, converting room temperature-stored platelets (RTSP) before their shelf-life expires to cold-stored platelets may be a good strategy for extending their shelf-life and addressing the platelet supply challenges, but the safety and comparative effectiveness of this strategy in bleeding patients has not been robustly assessed. This pilot study will assess the feasibility of conducting a definitive comparative study of standard room temperature-stored platelets (RTSP) and delayed cold-stored platelets (DCSP).

Platelet transfusion is the primary therapy for platelet-related bleeding (i.e., excessive bleeding due to platelet deficiency or dysfunction). Platelets are one of the most commonly used blood products, particularly in major cardiothoracic surgery with cardiopulmonary bypass where platelet deficiency and dysfunction occur in all patients to varying degrees [1, 2]. As a result, approximately one in four cardiac surgical patients receive at least one platelet transfusion to treat active bleeding in the operating room or soon thereafter, with high levels of variability across institutions. Approximately 10% of the total platelet supply is directed to cardiac surgery alone [3–5]. Since the 1970s, standard international practice has been to store platelet units at room temperature (20–24 °C). This preserves the longevity of platelets post-transfusion but limits their storage shelf-life to 7 days for both pooled buffy-coat bacterially cultured and pooled buffy-coat pathogen-inactivated platelets [6]. The short shelf-life of room-temperature platelets (RTP) creates major supply challenges for blood suppliers and hospitals and leads to wastage of up to 30% of platelet units due to outdating [7]. Additionally, existing data suggests that storage at room temperature, while prolonging circulatory survival after transfusion, may in fact impair hemostatic function [8].

Alternatively, platelets may be stored at 1–6 °C, referred to as cold-stored platelets (CSP). It has long been known that cold storage of platelets extends their shelf-life (potentially up to 21 days) and reduces the risk of bacterial contamination while maintaining platelet activity and function. Of interest, when platelets are chilled, their metabolic rate is decreased and metabolic substrates (e.g., glucose, lactate) required for energetically demanding hemostatic functions are better preserved [9]. The cumulative structural, metabolic, and molecular changes observed suggest that cold-stored platelets are ‘primed’ for hemostatic activity, and may therefore trigger more rapid formation of lysis-resistant clots than platelets stored at room temperature [8, 10–17]. This altogether suggests that CSP may be superior to conventional room temperature platelets for the management of acute surgical bleeding.

Given that diverting even a small fraction of freshly collected platelets to cold storage would further limit an already strained platelet supply, scientists at Canadian Blood Services (CBS) and elsewhere [18] have investigated refrigerating standard RTP several days after collection to produce delayed cold-stored platelets (DCSP) [9, 19]. Several investigators have shown that DCSP retains an acceptable metabolic and hemostatic profile compared with platelets cold-stored immediately after collection [7, 9, 20]. Overall, shifting platelets from room temperature to cold storage by the end of the 4th day appears to represent an ideal balance between quality preservation and supply maximization [20] that warrants clinical investigation.

Our central hypothesis is that compared to conventional room-temperature platelets, delayed cold-stored platelets have a non-inferior safety profile (due to inhibition of bacterial growth at colder temperatures) and have non-inferior hemostatic efficacy in acutely bleeding surgical patients. In line with this hypothesis, we anticipate that cold-stored platelets will be logistically superior for blood banks as they can be placed in the fridge and do not require space on the agitator, thereby allowing for easier maintenance of ABO-identical stock. The proposed pilot study is designed to determine optimal trial procedures, including the provision and distribution of cold-stored platelets at participating hospitals, for a planned future definitive trial with the hypothesis/hypotheses outlined above. The *primary feasibility outcomes* are (1) adequate recruitment (defined as ≥ 15% of eligible patients recruited per centre per month); (2) adequate cold-stored platelet supply (defined as an appropriate product available at the time of surgery for ≥ 90% of patients randomized to the cold-stored platelet group); (3) adequate clinician adherence to randomization assignment (defined as > 90% of all patients are administered the assigned product).

## Methods

### Design

This protocol is based on reporting guidelines from the SPIRIT guideline for Standard Protocol Items for Clinical Trials [21], adapted as recommended when reporting protocols of feasibility trials [22].

PLTS-1 is a multicentre, randomized, active-control, blinded, internal pilot trial, using a conventional, parallel-group, two-armed design to be conducted at two study centers. The study will assess the feasibility of a possible future, definitive RCT designed to determine whether DCSPs are non-inferior to conventional RTP with respect to hemostatic effectiveness (total number of allogeneic blood products transfused within 24 h after CPB) and safety. The study will enroll approximately 150 patients to treat 50 adult (≥ 18 years old) patients undergoing at least moderately complex cardiac surgery with CPB and requiring platelet transfusion. Based on historical institutional data, approximately 30% of patients undergoing complex surgery will require platelet transfusion [23]. We will explore the feasibility of the definitive RCT protocol with respect to participant recruitment, the ability of hospital blood banks to supply ABO-identical DCSP and clinician adherence to randomization assignment. If we proceed to the larger trial with no protocol changes or with protocol changes that can be reasonably expected to not impact the primary endpoints of the definitive trial (as determined by the study steering committee with recommendations from the IDSMC taken into account), the relevant outcome data from the pilot study will contribute to the definitive trial’s dataset thereby establishing this as an internal pilot. A diagram of the proposed study and the outcome assessment is provided in Fig. 1 and Table 1.

**Fig. 1 Fig1:**
[figure not shown]
Study flow

**Table 1 Tab1:** Flow chart of assessments performed throughout the study

Procedures	Before surgery	Surgery	Each platelet administration	POD-1	POD-7 or DC	POD-30
Obtain consent	X					
Inclusion and exclusion criteria	X					
Randomization criteria			x^b^			
Treatment criteria			x			
Platelets stored	X					
Intervention administered			x			
Baseline data						
Demographics	X					
Medical history	X					
Concomitant medications	X					
Surgical data						
Procedure details, date	X					
Intraoperative medications		x				
CPB time		x				
Transfusion data						
Platelets			x	x	x	x
Red cells				x	x	x
Plasma				x	x	x
Hemostatic agents				x	x	
Laboratory assessments						
Complete blood count	X	x	x	x	x	X
Platelet count (total, functioning)	X	x	x			
Coagulation profile ^a^		x	x			
Chemistry	X	x	x	x	x	X
Hematology	X	x	x	x	x	X
Safety labs	X	x	x	x	x	x
Bleeding						
Bleeding severity scale			x			
Chest tube output			x	x		
UDPB				x		
Additional endpoints						
Ventilation time				x	(x)	(x)
Duration of ICU stay				x	(x)	(x)
Hospital length of stay					x	(x)
All-cause mortality				x	(x)	(x)
AEs and SAEs				x	x	x
Treatment-emergent events				x	x	x
Quality of life	X					x
Unblinding			x		x	

*AEs* Adverse events, *CPB* Cardiopulmonary bypass, *DAOH* days alive and out of hospital, *DC* discharge, *ICU* intensive care unit, *POD* postoperative day, *SAEs* serious adverse events, *UDPB* universal definition of perioperative bleeding

() if needed

^a^Activated clotting time, PT, aPTT, INR, fibrinogen activity via Clauss assay, ROTEM EXTEM CT, ROTEM EXTEM MCF, ROTEM FIBTEM MCF, thrombin generation

^b^Only for first platelet administration

### Setting

The pilot will take place at two Canadian academic tertiary care centers with major cardiac surgical programs, Toronto General Hospital (Toronto, Ontario) and Kingston Health Sciences Centre (Kingston, Ontario).

### Eligibility criteria

Adult (≥ 18 years old) patients undergoing elective cardiac surgery with CPB will be eligible for inclusion if they are planning to undergo at least moderately complex surgery *or* have a preoperative platelet count ≤ 150,000 × 10^6^/L (this is a group at high risk of requiring platelet transfusions post-CPB) [2]. Moderately complex index surgery is defined as (i) repair/replacement of more than one valve; (ii) aorta (root/ascending/arch) replacement; (iii) any combination of coronary artery bypass grafting, valve repair/replacement, or aorta (root/ascending/arch) replacement; or (iv) re-do procedures consisting of a repair or revision of a prior cardiac intervention.

Patients will be excluded if DCSP are not going to be available at the time of surgery or if the patient (i) has a congenital or acquired hemostatic disorder (including platelet refractoriness due to anti-platelet and anti-human leukocyte antigen [HLA] antibodies) and/or requires specially matched platelets (including patients with anaphylaxis to blood due to Immunoglobulin A [IgA] deficiency with anti-IgA antibodies), (ii) has known contraindications to heparin, thereby excluding cases where non-reversible anticoagulants (i.e., argatroban) are used, (iii) is on warfarin or direct oral anticoagulants (dabigatran, rivaroxaban, apixaban or edoxaban) within 3 days prior to surgery, (iv) is on antiplatelet drugs within 5 days prior to surgery (excluding acetylsalicylic acid [ASA]), (v) refuses allogeneic blood products, (vi) has a known pregnancy, or (vii) is enrolled in another interventional clinical trial where routine care and management are altered, (vii) is hemodynamically unstable defined as critical care admission or vasopressor or inotrope dependence prior to index surgery, (viii) has a pre-operative requirement for, or expected post-operative dependence upon, mechanical circulatory support (i.e., intra-aortic balloon pump, ventricular assist device).

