### Recruitment

During the surgical preadmission visit, a member of the patient’s circle of care (e.g., surgeon, anesthesiologist, nurse) will invite all elective cardiac surgical patients meeting eligibility criteria to speak with a research coordinator about potential participation in the study. Interested patients will meet with a research coordinator who will provide study information and, where appropriate, obtain written informed consent prior to the scheduled surgical procedure. Thereafter, the research coordinator will contact the hospital blood bank to ensure the availability of adequate supplies of both types of platelets for each patient on the day of surgery (as randomization will only occur on the day of surgery but ABO-identical cold-stored platelets will be prepared a minimum of 24 h prior to the scheduled surgery—see “Randomization/assignment of interventions” section below).

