### Randomization/assignment of interventions

Recruited patients will only be randomized on the day of surgery if the clinical team places an order with the blood bank for platelet transfusion to treat active bleeding during the first 6 h after termination of CPB, and both platelet types are available (Fig. 1). When the platelet order is received, the blood bank technologist or assigned research coordinator will confirm the patient has consented to the study and is enrolled in the trial. The patient will then be randomized and the assigned product will be released [18, 24].

Patients will be randomly assigned (1:1 ratio) to study groups on the day of surgery using a permuted block, stratified (by center) allocation scheme prepared by a biostatistician not involved in the trial. Sequentially numbered sealed envelopes based on the randomization lists will be provided to the blood banks that will be providing the platelet product. This process, which has been successfully used in previous similar studies [25–28], has the advantage of allowing the technologists or coordinators to randomize patients as soon as the order is received without delaying therapy. The spot in the randomization list will not be reused if the patient assigned to it does not receive the platelet product. Once the order for the first platelet product is received and eligibility has been confirmed, the blood bank technologist will open the randomization envelope, and prepare and release the assigned platelet product in tamper-proof, temperature-stable containers that have been validated for this purpose and will be identical for each study arm. To maintain blinding, thermal gloves will be released by the blood bank for product handling and the product label (containing collection and expiration dates and type of platelet) will be obscured.

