### Outcomes

#### Primary feasibility endpoints

Adequate recruitment (defined as ≥ 15% of eligible patients enrolled per center per month to target consistent levels of enrollment) [33]Adequate cold-stored platelet supply (defined as appropriate product available at the time of surgery for ≥ 90% of patients randomized to the delayed cold-stored platelet group).Adequate clinician adherence to randomization assignment (defined as > 90% of all patients being administered the assigned product).

Recruitment and protocol adherence are key common progression criteria for internal pilots of efficient RCTs and ensuring adequate supply of cold-stored platelets is a critical metric for ensuring feasibility of the definitive trial. If all primary feasibility endpoints are met, we will proceed with the larger trial. If 1–2 of 3 feasibility endpoints are met, we will decide if the trial is feasible with modifications to the protocol addressing the specific deficiencies in trial design identified in the pilot. The trial will be considered infeasible if all primary feasibility endpoints fall short of their targets and can not be addressed with modifications to the study protocol. We will hold an investigator meeting to examine the type and number of major deviations, and to define protocol changes required based on the feasibility outcomes.

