### Statistical considerations

The pilot trial will randomize 50 adult (≥ 18 years old) patients undergoing at least moderately complex cardiac surgery with CPB and requiring platelet transfusion. Because the decision to administer platelets occurs intraoperatively but informed consent must be obtained pre-operatively, we will need to consent and enroll a larger sample of approximately 150 eligible patients, as we expect 30–40% of enrolled patients to receive platelets based on historical institutional transfusion practices [23]. This is also the ratio we have observed in similarly designed ongoing RCTs being conducted in this patient population (NCT05523297).

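### The recruitment denominator depends on cold-platelet supply and its counting rule is not fixed, so a shortage can be hidden from, raise or lower the ≥ 15% result

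*Protocol article*

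**What the plan says.** Cold-platelet availability enters the Methods of the protocol article at three points.

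- *Eligibility criteria*, at the head of the exclusions: "Patients will be excluded if DCSP are not going to be available at the time of surgery".
- *Recruitment*: a member of the care team "will invite all elective cardiac surgical patients meeting eligibility criteria to speak with a research coordinator". Written consent comes next, and the sequence then continues: "Thereafter, the research coordinator will contact the hospital blood bank to ensure the availability of adequate supplies of both types of platelets".
- *Randomization/assignment of interventions*: a patient is randomized only if platelets are ordered for active bleeding in the first 6 h after bypass "and both platelet types are available".

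The recruitment criterion in *Primary feasibility endpoints* is at least 15% "of eligible patients enrolled per center per month to target consistent levels of enrollment". The Abstract and the end of the Background use the same denominator. Enrollment means consent before surgery, not randomization: according to *Statistical considerations*, "we will need to consent and enroll a larger sample of approximately 150 eligible patients" in order to randomize 50.

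The supply criterion asks for product to be available for at least 90% "of patients randomized to the delayed cold-stored platelet group". *Statistical analysis* says that feasibility decisions compare point estimates with the targets.

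**The concern.** Recruitment is meant to show what share of suitable patients can be brought into the definitive trial. If lack of product makes a patient ineligible, that share is taken over a group whose size depends on the blood bank. The article also does not settle when the exclusion is applied. Patients are invited because they meet the eligibility criteria, yet one criterion turns on information that is described as sought only after consent. It is never determined for those who decline, and a patient already counted as enrolled may later meet an exclusion. The article does not say whether such a patient stays in the numerator, the denominator, both or neither.

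This is a progression criterion judged on a point estimate, so an open counting rule can change the decision. The supply criterion does not make up for it, because its denominator is formed after a check that both products are on hand.

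**Working it through.** **The plan's own figures.** The 15% target is a set threshold with no derivation, so there is nothing to reproduce. The neighbouring enrollment figure is consistent: 150 × 30% = 45 and 150 × 40% = 60, with 150 × 1/3 = 50.

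**Inputs.** Let c be the consent rate among clinically eligible patients who are approached, and u the share for whom no cold product is available. The article gives neither. Both are assumed, and availability is taken to be unrelated to willingness to consent. The illustration uses c = 20% and u = 30%, per 100 clinically eligible patients.

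**Counting rules**

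| Rule | Formula | Count | Result | Against 15% |
|---|---|---|---|---|
| A. All clinically eligible in the denominator; no-supply patients not approached | c(1 − u) | 14/100 | 14.0% | misses |
| B. No-supply patients screened out before approach, absent from both counts | c(1 − u)/(1 − u) = c | 14/70 | 20.0% | meets |
| C. Checked after consent; the 6 consenters without product leave both counts | c(1 − u)/(1 − cu) | 14/94 | 14.9% | misses |
| D. Checked after consent; the 6 leave the denominator but stay counted as enrolled | c/(1 − cu) | 20/94 | 21.3% | meets |

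In C and D the 80 decliners stay in the denominator, because their supply status is never checked.

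**Direction as the shortage grows** (c = 20%; u = 20%, 30%, 40%)

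- A: 16.0%, 14.0%, 12.0%
- B: 20.0%, 20.0%, 20.0%
- C: 16.7%, 14.9%, 13.0%
- D: 20.8%, 21.3%, 21.7%

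B is insulated from the shortage, C falls with it, and D rises slightly. Under B, a result of exactly 15% corresponds to 15% × (1 − u) of clinically eligible patients: 12%, 10.5% and 9% at these three values of u.

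**When the rule decides the outcome.** At u = 30%, B meets the target once c ≥ 15%, whereas A needs c ≥ 0.15/0.7 = 21.4%. Outside roughly that band the choice matters little. At c = 12% the four results are 8.4%, 12.0%, 8.7% and 12.4%, and all miss. At c = 25% they are 17.5%, 25.0%, 18.9% and 27.0%, and all meet.

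**Supply endpoint.** Its denominator is patients randomized to cold-stored platelets. Randomization takes place only when both products are available, so first-dose availability is close to guaranteed for everyone counted. A patient lost to shortage before randomization does not enter it. If that patient also drops out of the recruitment denominator, or has already been counted as enrolled, the loss shows in neither criterion.

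**The case against.** The strongest reply is that the three sections can be read in sequence. The exclusion looks ahead to a foreseeable lack of product, the post-consent contact is provisioning rather than an eligibility test, and the check at the platelet order is the final gate. Other exclusions, such as recent anticoagulant or antiplatelet use and instability before surgery, also cannot be settled at the preadmission visit. It is also defensible to keep supply out of the recruitment percentage when supply has its own endpoint. Finally, the full protocol may define the denominator, and the study-flow figure is not shown.

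Much of this stands. Completing eligibility after consent is not peculiar to this criterion, and the sequential reading is possible. But it leaves the counting open: a foreseeable gap found before approach gives rule B, and one found after consent gives C or D. The other exclusions describe the patient, whereas this one describes the supply that the pilot is meant to test. The separate supply endpoint does not fill the gap, because it is conditional on availability. The exclusion, the denominator and the order of steps are all stated in the article itself, so their fit is a fair question even if the full protocol resolves it.

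A reader might go further and infer that shortage makes the target easier, so that a poorly supplied center shows the better percentage. The documents do not support that in general. A check made only after consent reaches consenters alone, and if they leave both counts the rate falls. Screening before approach holds the rate at the consent rate; it looks high only beside a supply-independent denominator. A large rise, such as 20/70 = 28.6%, needs every no-supply patient removed from the denominator, decliners included, while every consenter stays in the numerator. The procedure described does not produce that.

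**Conclusion.** The point holds as an undefined, supply-dependent denominator in a progression criterion. It does not hold as a demonstrated bias towards passing. Under the assumed 20% consent and 30% without product, the three ways of applying the exclusion give 14.9%, 20.0% and 21.3%, against 14.0% for a supply-independent denominator with no-supply patients not approached. These lie on both sides of 15%. The size rests wholly on the assumed c and u, and the rule is decisive only when the consent rate is near the target. What does not depend on those values is that a shortage before randomization can be missing from the recruitment result and is largely invisible to the supply result. The comparison of the two platelet products is not affected. The wording should be corrected because it bears on the decision to proceed.

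**What to change.** In the Abstract, the Background and *Primary feasibility endpoints*, define the recruitment denominator as all patients meeting the clinical inclusion and exclusion criteria at screening, whether or not cold-stored product is available. Define the numerator as those who consent.

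In *Eligibility criteria*, take availability out of what makes a patient eligible. Treat it as an operational condition for approach and, as *Randomization/assignment of interventions* already has it, for randomization. Sites need not approach patients known to have no product; they need only count them.

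Keep patients who are not approached, or who later cannot be randomized, for lack of product in the denominator, and report their number by center with that reason code. The code is needed as well as the new denominator: where no-supply patients are approached and consent, they count as recruited, and the percentage alone would not show the shortage.

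The cost is a change of wording and one reason code in the screening log. The reported recruitment percentage may be somewhat lower. Who can be randomized does not change.
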